## Abstract

**Introduction:** The On&Out study is aimed at assessing the effectiveness, cost-utility and physiological underpinnings of the FIBROWALK multicomponent intervention conducted in two different settings: online (FIBRO-On) or outdoors (FIBRO-Out). Both interventions have proved to be efficacious in the short-term but there is no study assessing their comparative effectiveness nor their long-term effects. For the first time, this study will also evaluate the cost-utility (6-month time-horizon) and the effects on immune-inflammatory biomarkers and Brain-Derived Neurotrophic Factor (BDNF) levels of both interventions. The objectives of this 6-month, randomized, controlled trial (RCT) are 1) to examine the effectiveness and cost-utility of adding FIBRO-On or FIBRO-Out to Treatment-As-Usual (TAU) for individuals with fibromyalgia (FM); 2) to identify pre–post differences in blood biomarker levels in the three study arms and 3) to analyze the role of process variables as mediators of 6-month follow-up clinical outcomes.

**Methods and analysis:** Participants will be 225 individuals with FM recruited at Vall d’Hebron University Hospital (Barcelona, Spain), randomly allocated to one of the three study arms: TAU vs. TAU + FIBRO-On vs. TAU + FIBRO-Out. A comprehensive assessment to collect functional impairment, pain, fatigue, depressive and anxiety symptoms, perceived stress, central sensitization, physical function, sleep quality, perceived cognitive dysfunction, kinesiophobia, pain catastrophizing, psychological inflexibility in pain and pain knowledge will be conducted pre-intervention, at 6 weeks, post-intervention (12 weeks), and at 6-month follow-up. Changes in immune-inflammatory biomarkers [i.e., IL-6, CXCL8, IL-17A, IL-4, IL-10, and high-sensitivity C-reactive protein (hs-CRP)] and Brain-Derived Neurotrophic Factor will be evaluated in 40 participants in each treatment arm (total n = 120) at pre- and post-treatment. Quality of life and direct and indirect costs will be evaluated at baseline and at 6-month follow-up. Linear mixed-effects regression models using restricted maximum likelihood, mediational models and a full economic evaluation applying bootstrapping techniques, acceptability curves and sensitivity analyses will be computed.

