### 2.3 Sample size calculation

Two-hundred and twenty-five individuals who meet the selection criteria for the study will be recruited. The estimated sample size needed is n = 63 participants per condition considering a moderate effect size (Cohen’s d = 0.5) for the difference between the active arms at post-intervention compared to the control group for the primary variable (i.e., FIQR score) with an alpha = 0.05 and 1-b power = 0.80. With an expected dropout rate of 20%–25%, the final sample size is estimated at 75 individuals per arm. The effect size used for the sample size calculation corresponds to the average effect size for multicomponent interventions in FM vs. control group (Nüesch et al., 2013). Previous RCTs evaluating the FIBROWALK intervention indicated effect sizes between d = 0.4 (Serrat et al., 2021a) and d = 1.83 (Serrat et al., 2020). Using as a reference previous studies of the group evaluating the effect of different non-pharmacological treatments in FM patients on blood values of immuno-inflammatory markers (Andrés-Rodríguez et al., 2019; Montero-Marin et al., 2020), it is estimated that a sample size of 40 subjects per arm will be sufficient to be able to detect changes in the evaluated variables.

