### 2.5 Procedure and randomization

The recruitment of participants will be carried out in two ways: 1) consecutive recruitment from consultation by the rheumatologists of the HUVH Central Sensitivity Syndromes Specialized Unit and 2) by screening a list of patients (with contact telephone number) corresponding to patients who contacted the Unit during the last 6 months. The clinicians involved in the project (i.e., MA and MS) will proceed to carry out the telephone screening and those who meet the selection criteria of the study will be invited to participate. After obtaining written informed consent, the instrument battery -including clinical and economic measures-described below will be administered (online assessment). Two research assistants will coordinate the study assessments to ensure an adequate understanding of all administered self-reported measures. Random assignment of participants to study arms will be executed after baseline assessments as recommended by the CONSORT guidelines (Schulz et al., 2010). Once written consent and baseline assessment have been completed, study participants will be given a unique personal code and randomized using randomization software (1:1:1 ratio). The computer-generated randomization will apply a permuted block design to ensure that the groups are balanced taking biomarkers substudy eligibility criteria (No=Not meeting criteria for biomarkers substudy; Yes = Meeting criteria) into account. The randomization list will be stored in an encrypted file on a password-protected computer in the clinical trials supervisor’s office to assure concealment of allocation. Participants will be informed of their group allocation by the administrative personnel, who will send a notification *via* email.

Patients who meet the selection criteria for the biomarkers substudy will be rescheduled 3–5 days after the first assessment to obtain blood samples (up to the required N of 40 subjects per arm). Fasting blood extractions will be performed in a pre-set time window (8a.m.–10a.m.) to reduce circadian variability in the levels of the biomarkers evaluated. In order to limit the effects of medication on the study variables, patients will be asked to refrain from taking any occasional anti-inflammatory drugs in the 72 h prior to blood sampling.

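### The biomarker substudy uses 40 per arm as the size needed, the cap on baseline blood draws and the number evaluated at both visits, with no allowance for the dropout the plan itself expects

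*Protocol article*

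**What the plan says.** Section 2.3 (Sample size calculation) justifies the substudy by reference to the group's earlier studies and concludes that "it is estimated that a sample size of 40 subjects per arm will be sufficient to be able to detect changes in the evaluated variables". It gives no effect size, standard deviation, alpha or power for the biomarkers.

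Section 2.5 (Procedure and randomization) sets the number of patients recalled for the first blood sample: "up to the required N of 40 subjects per arm". The Abstract says that the biomarkers "will be evaluated in 40 participants in each treatment arm (total n = 120) at pre- and post-treatment".

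For the main trial, Section 2.3 starts from 63 per arm and then allows for attrition: "With an expected dropout rate of 20%–25%, the final sample size is estimated at 75 individuals per arm". That calculation is "for the difference between the active arms at post-intervention compared to the control group for the primary variable". Post-intervention is week 12, the visit at which the second blood sample is taken (Table 3).

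Section 2.11.4 plans a REML mixed model for the biomarkers. Section 2.10 gives, among the reasons for sampling at these two visits, the use of pre–post change as a mediator of 6-month outcomes. Section 2.11.2 excludes participants with missing data from the mediation analyses.

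**The concern.** One number does three jobs: the size called sufficient, the ceiling on baseline draws, and the count evaluated at both visits. These agree only if nobody is lost between baseline and week 12. The same sample size section expects 20%–25% loss among the patients from whom the substudy is drawn, and acts on it for the main sample only.

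A patient with no baseline sample cannot supply a pre–post pair later, so the cap on first draws limits the number of pairs. Pre–post biomarker change is the trial's second objective, and the biomarkers are candidate mediators under the third. If fewer than 40 pairs per arm are available, the statement that 40 is sufficient no longer describes the data analysed, and a null biomarker result could be read with more confidence than the design supports.

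**Working it through.** **Inputs.** 40 per arm (Section 2.3; cap in Section 2.5; both visits in the Abstract). Dropout 20%–25% (Section 2.3). 75 randomised per arm (Section 2.3). Alpha 0.05 and power 0.80 are stated for the main trial only, with sidedness not given.

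**The plan's own figures.** The 40 per arm cannot be reproduced, because no effect size or power accompanies it. The main-trial figure can: with d = 0.5, two-sided alpha 0.05 and power 0.80, n = 2(1.96 + 0.84)²/0.5² = 62.7, so 63 per arm, as stated. A one-sided test would give 50. Going from 63 to 75 accommodates 1 − 63/75 = 16% loss.

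**Pairs left from 40 baseline samples**, 40 × (1 − loss):
- 20%: 40 × 0.80 = 32 per arm, 96 in total
- 25%: 40 × 0.75 = 30 per arm, 90 in total
- 16%, the loss that 63 to 75 accommodates: 40 × 0.84 = 33.6 per arm
- 10%, assumed: 40 × 0.90 = 36 per arm, 108 in total

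The Abstract's total is 120. Since 40 is an upper limit on first draws, each figure is a maximum for its loss rate, unless lost patients are replaced.

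**If first-period losses were replaced in the second period.** Section 2.5 runs the study in two consecutive periods. Assume 20 baseline samples per arm in each, with every first-period loss made up by an extra second-period draw:
- 20%: 20 × 0.80 + (20 + 4) × 0.80 = 16 + 19.2 = 35.2
- 25%: 20 × 0.75 + (20 + 5) × 0.75 = 15 + 18.75 = 33.75

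So about 34–35 pairs remain, still below 40.

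**Illustrative cost in power.** Two-arm comparison, two-sample t test, two-sided alpha 0.05. At 40 per arm, 80% power corresponds to d = 0.63. Holding that effect fixed:

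| Per arm | Power at d = 0.63 | d detectable with 80% power |
|---|---|---|
| 40 | 80% | 0.63 |
| 36 | 76% | 0.67 |
| 32 | 70% | 0.71 |
| 30 | 68% | 0.74 |

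At the main trial's d = 0.5, used here only as an assumption, power is 60% with 40, 50% with 32 and 48% with 30. None of these d values is the plan's own.

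**Baseline draws needed to keep 40 pairs**, 40/(1 − loss): 40/0.80 = 50 and 40/0.75 = 53.3, so 50–54 per arm. That is 50/75 = 67% to 54/75 = 72% of each randomised arm.

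**The case against.** The strongest reply is that inadequacy has not been shown. Section 2.3 speaks of subjects, not completed pairs, and rests on earlier studies that are not reproduced. The 40 might already contain a margin, or 30–32 might be enough. This stands in part: a reader might infer that the substudy is underpowered, and the article does not support that, because it gives no biomarker effect size or power. But nothing mentions a margin, and Section 2.5 calls 40 the required number while the Abstract places 40 at both visits.

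Second, the visit to which 20%–25% applies is not stated. It is attached to a post-intervention calculation, but Section 2.10 expects less sample loss at post-intervention than at 6 months, and the Discussion cites adherence above 90% in earlier studies. So 30–32 is the result at the plan's own rate if it applies by week 12, not a forecast. Any loss still leaves fewer than 40 of the first 40.

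Third, the two-period design leaves room for replacement. A reader might infer that no lost patient can be made up; the article does not rule it out. It states no such rule, and the version tried above would still fall short.

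Fourth, REML keeps patients with only a baseline sample, so the t approximation may overstate the loss. This is fair for the biomarker model, although such patients add little information on change. It does not help the mediation analyses, which drop them.

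Fifth, an article may leave a substudy attrition rule to the full protocol. The point, however, is that three stated uses of one number do not fit the stated dropout.

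A reader might also expect further loss because Section 2.4 excludes patients with infection symptoms or recent vaccination. That follows only if those criteria are applied again at week 12 and the draw is forfeited rather than delayed, which the article does not say.

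**Conclusion.** The point holds as a mismatch between stated figures: 40 per arm cannot be both the ceiling on baseline draws and the number evaluated at both visits when the plan expects dropout. At 20%–25% loss by week 12, at most 30–32 pairs per arm remain; at an assumed 10%, 36; with the assumed replacement in the second period, about 34–35. The illustrative cost is a fall from 80% to about 68%–70% power (76% at 36 pairs), resting on a two-sample t approximation rather than the planned mixed model. The primary FIQR analysis is unaffected. The change should be made because the biomarkers carry a stated objective and feed the mediation models, and because correcting the statement is cheap.

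**What to change.** Either of two changes would reconcile the figures.

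(a) In the Abstract and Section 2.3, state up to 40 baseline samples per arm and about 30–32 expected pre–post pairs at the plan's dropout rate, and rest the sufficiency statement on the number of pairs. This costs wording only, with a less favourable figure. The detectable d values above should not be entered as the plan's own; any such figure needs the biomarker assumptions that the sponsor actually used.

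(b) If enough of the 75 per arm meet the substudy criteria, raise the cap in Section 2.5 to 50–54 baseline samples per arm, among patients already being randomised. This needs 67%–72% of each arm to be eligible, a share the article does not give; if fewer qualify, (a) applies. The cost is 10–14 extra draws per arm, plus one of two things: extra assays, against the budget limits mentioned in Section 2.10, or, if only complete pairs are assayed, the loss of baseline-only data that the REML model could use. That choice should be stated.

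Under either option, one sentence should say whether a patient lost before week 12 still counts towards the cap.

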### 2.4 Eligibility criteria

All participants will meet the following general inclusion criteria: 1. Individuals between 18 and 65 years of age. 2. Diagnosis of FM according to the ACR 2010/2011 criteria. 3. Understanding written and spoken Spanish. The general exclusion criteria will be: 1. Psychological treatment received within the last year or current. 2. Comorbid presence of severe mental disorder (e.g., schizophrenia) or other terminal clinical conditions or scheduled treatments that may interrupt study follow-up. 3. Inability to complete the weekly sessions/modules of the program on a regular basis.

For the biomarkers substudy, usual contraindications for measuring blood immune-inflammatory markers will be taken into account to establish the following additional inclusion/exclusion criteria for the biomarkers substudy: only participants of female sex, with no autoimmune-type disease, no recent physical trauma, not being vaccinated during the last week, no symptoms suggestive of cold/infection on the day of blood collection, no needle phobia, not pregnant or breastfeeding, not using oral or local corticosteroids or any anti-cytokine biologic drugs or oral contraceptives will be included in the biomarkers substudy.

### 2.5 Procedure and randomization

The recruitment of participants will be carried out in two ways: 1) consecutive recruitment from consultation by the rheumatologists of the HUVH Central Sensitivity Syndromes Specialized Unit and 2) by screening a list of patients (with contact telephone number) corresponding to patients who contacted the Unit during the last 6 months. The clinicians involved in the project (i.e., MA and MS) will proceed to carry out the telephone screening and those who meet the selection criteria of the study will be invited to participate. After obtaining written informed consent, the instrument battery -including clinical and economic measures-described below will be administered (online assessment). Two research assistants will coordinate the study assessments to ensure an adequate understanding of all administered self-reported measures. Random assignment of participants to study arms will be executed after baseline assessments as recommended by the CONSORT guidelines (Schulz et al., 2010). Once written consent and baseline assessment have been completed, study participants will be given a unique personal code and randomized using randomization software (1:1:1 ratio). The computer-generated randomization will apply a permuted block design to ensure that the groups are balanced taking biomarkers substudy eligibility criteria (No=Not meeting criteria for biomarkers substudy; Yes = Meeting criteria) into account. The randomization list will be stored in an encrypted file on a password-protected computer in the clinical trials supervisor’s office to assure concealment of allocation. Participants will be informed of their group allocation by the administrative personnel, who will send a notification *via* email.

Patients who meet the selection criteria for the biomarkers substudy will be rescheduled 3–5 days after the first assessment to obtain blood samples (up to the required N of 40 subjects per arm). Fasting blood extractions will be performed in a pre-set time window (8a.m.–10a.m.) to reduce circadian variability in the levels of the biomarkers evaluated. In order to limit the effects of medication on the study variables, patients will be asked to refrain from taking any occasional anti-inflammatory drugs in the 72 h prior to blood sampling.

The research assistants, who will be blinded to randomization, will coordinate the three subsequent clinical assessments: at 6 weeks, at post-intervention and at 6 months after the baseline assessment (follow-up). The same procedure as in baseline will be followed for the collection of biological samples at post-intervention, respecting the pre-set time interval.

The study will be organized in two consecutive periods with six study groups (i.e., 2 TAU, 2 FIBRO-Out, 2 FIBRO-On) conducted in parallel in each period. All the groups will include 18–20 participants (i.e., FIBRO-On, FIBRO-Out, TAU), so the N = 75 is expected to be reached at the end of the study.

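### The protocol does not secure that baseline blood for the biomarker substudy is taken before randomisation and allocation notice, and its per-arm cap and day-of-draw criteria do not fit together under either order

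*Protocol article*

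**What the plan says.** All of this is in Section 2.5 of the protocol article unless stated.

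- **First contact.** After consent, "the instrument battery -including clinical and economic measures-described below will be administered (online assessment". It is a set of questionnaires; blood is not part of it.
- **Randomisation.** The rule is given twice: "Random assignment of participants to study arms will be executed after baseline assessments as recommended by the CONSORT guidelines", and "Once written consent and baseline assessment have been completed, study participants will be given a unique personal code and randomized using randomization software".
- **Stratum.** Randomisation uses a "permuted block design to ensure that the groups are balanced taking biomarkers substudy eligibility criteria" into account, coded Yes or No.
- **Notice of allocation.** "Participants will be informed of their group allocation by the administrative personnel, who will send a notification" by email. Its timing relative to the blood draw is not given.
- **Blood.** In the next paragraph, women who meet the substudy criteria "will be rescheduled 3–5 days after the first assessment to obtain blood samples (up to the required N of 40 subjects per arm".
- **Substudy criteria (Section 2.4).** They include "not being vaccinated during the last week, no symptoms suggestive of cold/infection on the day of blood collection".
- **Label and size.** Section 2.8, Table 3 and Section 2.10 call the first sample a baseline measure. The abstract gives 40 per arm, 120 in total.

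**The concern.** The substudy is meant to give a randomised comparison of biomarker change between three arms, and balancing the randomisation on substudy eligibility serves that purpose. The balance holds only if membership of the substudy is settled before the arm is known.

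Read in the order in which it is written, Section 2.5 leaves membership open after allocation. Participants are not blinded (Section 2.13). A woman told that she is in TAU, or in the format she did not want, may be less willing to attend an extra fasting visit between 8 and 10 a.m. A day-of-draw criterion can remove her after she was randomised as eligible. No rule says which 40 are taken if more qualify.

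At stake are objective 2 (biomarker change and its correlation with clinical change) and the use of biomarkers as mediators in objective 3.

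**Working it through.** **1. The stated size.** 3 × 40 = 120, which agrees with the abstract. No effect size, SD, alpha or power is given for the 40 per arm, so it cannot be reproduced further. The cap is 40/75 = 53% of an arm. It selects a subset only if more than 40 women per arm are eligible, and the number eligible is not given.

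**2. The two possible orders, set against the text.**

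| | Blood after allocation | Blood before allocation |
|---|---|---|
| Order of the text in Section 2.5 | Fits | Does not follow it, but does not contradict it |
| Cap of 40 per arm | Can be applied to individuals | Cannot be applied: no arm exists yet. Works only as 120 in total |
| Randomisation follows baseline assessments | Fits only if baseline means the online battery alone | Fits |
| Blood labelled as baseline | Fits only as pre-treatment | Fits |
| Eligibility stratum coded before randomisation | Cannot be final: symptoms on the day of collection are not yet known, and vaccination in the last week can change within 3–5 days | Can be final, if coded at the blood visit |

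Each column has at least one entry that fails, so Sections 2.4 and 2.5 have to be reconciled whichever order is intended.

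**3. What an after-allocation draw could do.** The documents give no attendance figures, so this is an illustration on assumed inputs:

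- full attendance in the active arms;
- attendance in TAU of 60, 70 or 80%;
- TAU attendance rising with symptom severity, at log-odds of 0.5 or 1.0 per SD;
- a correlation r of 0.3 or 0.5 between severity and the marker, both standardised.

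With severity S standard normal and attendance probability p(S) = 1/(1 + exp(−(a + bS))), a is set so that the mean of p(S) equals the attendance rate. The mean severity of attenders is E[S·p(S)]/E[p(S)], and the shift in the marker mean is r times that. By numerical integration:

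| TAU attendance | b | Shift in severity (SD) | Marker shift, r = 0.3 | Marker shift, r = 0.5 |
|---|---|---|---|---|
| 80% | 0.5 | 0.096 | 0.029 | 0.048 |
| 80% | 1.0 | 0.173 | 0.052 | 0.087 |
| 70% | 0.5 | 0.143 | 0.043 | 0.071 |
| 70% | 1.0 | 0.253 | 0.076 | 0.126 |
| 60% | 0.5 | 0.189 | 0.057 | 0.095 |
| 60% | 1.0 | 0.332 | 0.100 | 0.166 |

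The marker shift is 0.03 to 0.17 SD. A simulation of 400,000 draws from the same model gives 0.026 to 0.163, the same range within simulation error. If attendance depends on the marker itself (log-odds 0.25 to 0.5 per SD, attendance 70 to 90%), the shift is 0.03 to 0.15 SD.

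**4. Scale.** The standard error of a difference between two baseline means at 40 per arm is √(2/40) = 0.22 SD. A shift of this size would therefore not be detected by comparing baselines, and an equal 40/40/40 would not reveal it.

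**The case against.** The strongest reply is that nothing in the article says blood is drawn after randomisation. Randomisation follows baseline assessments, in the plural; biomarkers are listed among the baseline measures; and blood is timed from the first assessment, which may mean the first of several. Paragraph order in a condensed article does not fix visit order. The 40 per arm may be shorthand: 120 eligible women sampled before a 1:1:1 blocked randomisation would give about 40 in each arm. This stands as far as it goes, and it rules out stating the after-allocation draw as fact. It does not remove the conflict, because on this reading the cap as worded has no meaning before allocation.

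The mechanism is also partly conjecture. The article does not say that places are filled by order of attendance, that refusals are replaced, or that women restrict anti-inflammatory drugs differently by arm. That stands too: these are possibilities which the text leaves open, not procedures it sets out.

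Finally, the illustrated shift is smaller than the 0.22 SD standard error, and it is a shift in the baseline mean, not in change over time, which is what a mixed model with a group-by-time term estimates. This limits the point but does not dispose of it. Random imbalance is reflected in the confidence interval; selection is not. Selection on severity could also affect change, for example through regression to the mean, but that effect has not been calculated here.

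**Conclusion.** The concern holds as an unresolved conflict in the protocol. Section 2.5 does not secure that baseline blood precedes randomisation and the allocation email. Its order and its per-arm cap point to a later draw, while its baseline wording allows an earlier one.

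Two stronger readings are not supported. A reader might infer that blood is certainly drawn after allocation; no sentence says so. A reader might also infer that the baseline values are affected by treatment; nothing suggests that the first sample is taken after sessions begin, so even on the adverse reading the value may still be pre-treatment. The risk is who enters the substudy.

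The size cannot be derived from the documents. The 0.03 to 0.17 SD shift rests wholly on the assumed attendance pattern and correlation. The effect is confined to objective 2 and the mediation analyses that use biomarkers. The FIQR primary analysis, the clinical secondary outcomes and the cost-utility analysis are not touched. Severity is moderate, for the substudy only. It cannot be repaired once blood has been drawn, so it should be settled before recruitment starts.

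**What to change.** In Section 2.5, state this order for women who may enter the substudy:

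1. Complete the online baseline battery.
2. Attend the fasting blood visit in the planned 3–5 day window, before randomisation and before any notice of allocation.
3. Apply the day-of-draw criteria of Section 2.4 at that visit, and code the stratum Yes or No from the result.
4. Randomise, then send the allocation email.

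Replace the cap of 40 per arm with 120 sampled in total in the Yes stratum; the permuted blocks then give about 40 per arm. Once 120 are reached, code later recruits as not in the substudy. Report the numbers eligible, invited and sampled, by arm once randomised.

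The cost is small. Randomisation of these participants waits the 3–5 days already planned. A few samples may come from women who withdraw before randomisation, which wastes a sample but cannot depend on the arm. Arm sizes may differ slightly from 40.

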**Physical therapeutic exercises in the FIBROWALK program**
• Warm-up: activation and mobility exercises
• Therapeutic exercises: moderate aerobic-cardiovascular and muscle strengthening exercises combined with some balance and coordination exercises performed in a playful manner with cognitive and emotional targets (multitask works) where the level of difficulty and dedication time gradually increases
• Cooling-down: flexibility and relaxation exercises

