**Homework**
• Moderate intensity walking is recommended from the first session in a progressive pattern: 1st month - once per week, 2 nd month - twice per week, 3rd month - three times per week
• Exercises based on PNE, CBT and MT contents are also proposed every week (e.g., identifying danger signals, modifying sleep habits, challenging negative automatic thoughts, doing a 10-min body scan meditation)
• Double tasks: combining TE with CBT by fostering different cognitive/affective regulation skills throughout exercise (e.g., identifying external and internal stimuli which may promote positive affect during the exercise, discovering automatic thoughts during the exercise and uncovering patterns between thoughts with negative emotions, pain experience and fatigue; diminishing catastrophic thinking; recognizing the achievements, improving self-efficacy)

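### The blood-draw rules neither standardise nor record recent exercise, which at the post-intervention draw probably differs between the active arms and TAU

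*Protocol article*

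**What the plan says.** All references are to the Protocol article.

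- **Draw conditions (2.5).** "Fasting blood extractions will be performed in a pre-set time window (8a.m.–10a.m.) to reduce circadian variability", and "patients will be asked to refrain from taking any occasional anti-inflammatory drugs in the 72 h prior to blood sampling".
- **Substudy eligibility (2.4).** Further short-lived influences are excluded: "no recent physical trauma, not being vaccinated during the last week, no symptoms suggestive of cold/infection on the day of blood collection".
- **Timing of the baseline draw (2.5).** Eligible patients "will be rescheduled 3–5 days after the first assessment to obtain blood samples".
- **Post-intervention draw (2.5).** "The same procedure as in baseline will be followed for the collection of biological samples at post-intervention, respecting the pre-set time interval".
- **Exercise in the active arms (Table 1).** The programme contains "Therapeutic exercises: moderate aerobic-cardiovascular and muscle strengthening exercises combined with some balance and coordination exercises". Home walking is stepped up: "1st month - once per week, 2 nd month - twice per week, 3rd month - three times per week". FIBRO-Out sessions are weekly (2.6.3). FIBRO-On patients do each weekly module on a day they choose (2.6.2).
- **Exercise in TAU (2.6.1).** TAU is mainly pharmacological, usually with guidelines for aerobic exercise. No amount is given.
- **Data and model.** The home-practice log (2.9) covers the two active programmes and serves to measure adherence. The biomarker model (2.11.4) names one possible covariate, antidepressant status, added only if it shows a significant effect.
- **Use of the markers.** Objective 2 concerns pre–post differences in the markers, and objective 3 includes them as mediators of long-term improvement. Section 2.10 gives the use of pre–post change as a mediator of 6-month outcomes as one reason for the sampling schedule.

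**The concern.** The draw rules show that the sponsor wants to keep short-lived influences out of the marker levels. Food, time of day, occasional drugs, recent vaccination and infection are all dealt with. Recent exercise is not, although it is the one such influence that the randomised treatment itself changes.

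At baseline this does no harm on average, because no arm has started and randomisation balances exercise habits. By the second draw, the active arms have been advised to walk three times a week and have had weekly sessions with aerobic and strengthening work. TAU patients usually have general advice only. If a bout leaves any trace in the next morning's sample, the comparison with TAU combines that trace with whatever lasting change the programme has produced.

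This matters most for the mediation analysis. A mediator of 6-month outcomes is of interest as a change that persists, not as the residue of the last walk. The gap cannot be repaired afterwards: time since last exercise is not collected at the draw, and TAU has no practice log.

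**Working it through.** **1. The plan's own sample-size figures.** For the FIQR, section 2.3 gives d = 0.5, alpha 0.05 and power 0.80. Taking the test as two-sided, n = 2 × (1.960 + 0.842)² / 0.5² = 62.8, so 63 per arm, as stated. The 40 per arm for biomarkers has no stated effect size, SD or power and cannot be reproduced. For scale, at the same alpha and power, 40 per arm detects (1.960 + 0.842) × √(2/40) = 0.626 SD, or 0.634 SD with the t distribution. With 32 or 30 per arm (after 20% or 25% dropout) the normal-approximation figures are 0.70 and 0.72 SD.

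**2. How often a draw would follow a bout.** Assume k exercise days placed at random in the week and a draw on a random morning. Then P(bout within the previous w days) = 1 − C(7−w, k)/C(7, k).

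| Exercise days in the draw week | Previous day | Within 2 days | Within 3 days |
|---|---|---|---|
| 3 (walks continue, no session) | 3/7 = 43% | 1 − 10/35 = 71% | 1 − 4/35 = 89% |
| 4 (walks plus one session) | 4/7 = 57% | 1 − 5/35 = 86% | 1 − 1/35 = 97% |

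The 3 comes from Table 1. The fourth day counts only if a session still falls in the draw week. If walking stops with the programme, the figures are lower.

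**3. Possible bias.** Bias = (share exercised the day before, active − same share, TAU) × next-morning shift in SD units. Assumptions: TAU patients exercise on 0, 1 or 2 days a week; the shift is 0 to 0.5 SD in either direction; the after-effect is confined to the next morning. The documents supply none of these three.

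| Active vs TAU share | Shift 0 | 0.10 | 0.25 | 0.50 |
|---|---|---|---|---|
| 3/7 vs 2/7 | 0 | 0.01 | 0.04 | 0.07 |
| 4/7 vs 2/7 | 0 | 0.03 | 0.07 | 0.14 |
| 4/7 vs 1/7 | 0 | 0.04 | 0.11 | 0.21 |
| 3/7 vs 0 | 0 | 0.04 | 0.11 | 0.21 |
| 4/7 vs 0 | 0 | 0.06 | 0.14 | 0.29 |

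With some exercise in TAU the ceiling is 0.21 SD, and 0.21/0.634 = 34% of the detectable difference. With none it is 0.29 SD. These figures depend on the one-day assumption: an undiminished two-day after-effect of 0.5 SD with no exercise in TAU would give 0.86 × 0.5 = 0.43 SD.

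**4. Effect on the test.** Take no lasting effect, 40 per arm, and 43% to 57% of the active arm but none of TAU affected. A simple two-sided 5% comparison of means then rejects in about 5% to 6% of trials at a shift of 0.10 SD, 8% to 10% at 0.25 SD, and 16% to 25% at 0.50 SD.

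**The case against.** The strongest case against has five parts.

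- **The draw is post-intervention, not mid-programme.** This stands. A reader might infer that active-arm patients are sampled while the programme is running, but sections 2.5, 2.8 and 2.10 place the draw after it. If the baseline procedure includes the 3–5 day gap, it may fall later still. That gap, however, runs from the assessment and not from the last exercise. Section 2.5 leaves open whether it applies again, and walking may continue.
- **The mechanism is not in the documents.** This also stands. A reader might infer that an acute response is mixed into the treatment effect and hides falls in IL-6, CXCL8 or BDNF. No section gives a direction, size or duration for such a response, and the objectives state no directional biomarker hypothesis. The evidence in section 1.3 concerns effects of whole programmes. The bias range must therefore start at zero.
- **Exercise is part of the treatment.** A post-programme difference that includes an after-effect is still a valid randomised effect of assignment. That is right for the between-arm test, but less comfortable when the change is used as a mediator of 6-month outcomes.
- **A condensed article may leave draw instructions to the full protocol.** Fair in general, but this article sets out its draw rules in detail, down to hours, and exercise is not among them.
- **A strict rule would be costly.** Matching the 72 h drug rule would be breached by chance in 89% to 97% of adherent active-arm patients unless homework were moved in advance. This stands against a long interval, but not against a short, announced one.

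**Conclusion.** The point holds as a modest gap in measurement control. The plan neither standardises nor records recent exercise at the draws, and exercise probably differs between the active arms and TAU at the second one. Any after-effect of the last bout then cannot be told apart from a lasting change.

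The size is unknown from the documents. Under the stated assumptions the bias lies between 0 and about 0.2 SD, or up to 0.29 SD if TAU patients do not exercise, against about 0.63 SD detectable with 40 per arm. If the after-effect fades before the draw, the bias is near zero, but without recorded timing the investigators could not show this. The documents do not support saying that bias is present or which way it runs.

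The scope is the biomarker comparisons with TAU, including the inflammatory-balance indices, and the biomarker mediation. FIBRO-On versus FIBRO-Out is less exposed because the content is equivalent, although the time from last session to draw may still differ. The FIQR primary analysis and the cost-utility analysis are unaffected.

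**What to change.** In section 2.5, for both draws and all three arms:

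1. Add the same short exercise-free interval before the draw. The sponsor sets its length and announces it together with the existing drug instruction.
2. Record the date and time of last exercise at each draw.

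In section 2.11.4, report time since last exercise by arm at each draw. Any analysis restricted to draws that kept the rule should be labelled exploratory, because it selects patients on behaviour after randomisation and so loses the protection of the randomised comparison.

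The cost is one line in the appointment instructions and one recorded item. The downside is minor: some homework, or now and then a draw, has to be moved around the appointment.
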